##### 2.2.3.5 Data collection and follow-up

Nurses will record the information in the Research Electronic Data Capture application (REDCap). The follow-up will be conducted at the consultation or the patient's home and will comprise a period of 18 months for each participant or until their dropout. Variables will be collected at four time points, namely at the baseline and at 6, 12, and 18 months. To achieve comparability of the data collected, the same data collection notebook was used in all the participating centers, which also included validated questionnaires. In addition, all the professionals who collected data were trained in the use of the application and in the collection process in order to standardize the criteria.

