##### 2.2.3.2 Sample size

Based on the assumption of a proportional hazards model for survival times, the sample size was estimated to allow the comparison of two curves. The probability of a change in functionality of < 5 points at 18 months was previously estimated to be 47% in the unexposed group (22) and this figure was considered to decrease by at least 10% in exposed patients. Considering a ratio of 2:1 between the sample sizes of the unexposed and exposed groups, for a CI of 95%, a power of 80%, and a dropout rate of 20%, the sample size was calculated to be 1,035 subjects (690 unexposed and 345 exposed). A randomized sampling by quotas for the included health centers in each of the regions will be performed.

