##### 2.2.3.4 Variables

The exposure variable will be SARS-CoV-2 infection confirmed by diagnostic testing between May 11th of 2020 and the recruitment start date. The outcome variables will be mortality, functionality (Barthel scale), quality of life (EuroQol-5D), mental health (Hamilton depression rating scale), cognitive capacity (Mini-Mental State Examination), and frailty (Frailty index). In addition, sociodemographic (age and gender) and clinical, infection-related, and pandemic-context variables will be recorded. The date of the infection diagnosis and length of hospitalization will also be recorded for the cohort of exposed patients, as well as diagnoses of infection during the follow-up for the cohort of unexposed patients.

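### The 18-month cohort ends follow-up at dropout for every outcome, mortality included, and names no later check of vital status, so informative dropout may bias its results

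*Protocol article*

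**What the plan says.** Section 2.2.3.5 of the protocol article states that follow-up "will comprise a period of 18 months for each participant or until their dropout". On timing it says: "Variables will be collected at four time points, namely at the baseline and at 6, 12, and 18 months". On place it says: "The follow-up will be conducted at the consultation or the patient's home".

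Section 2.2.3.4 opens its list of outcomes with "The outcome variables will be mortality, functionality (Barthel scale" and goes on to quality of life, depression, cognition and frailty. Section 2.2.3.2 gives 1,035 subjects (690 unexposed, 345 exposed), calculated "for a CI of 95%, a power of 80%, and a dropout rate of 20" per cent. Section 2.2.3.6 plans Kaplan-Meier curves with the log-rank test for the main variables, and Cox models at 6, 12 and 18 months.

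The article does not define dropout. For this cohort it names no source of death dates or of functional status after dropout. Section 2.2.3.1 makes living outside an institution a condition of entry and excludes people transferred during recruitment. It is silent on moves during follow-up. Section 3 expects the assigned nurses to keep dropout low. Section 3.1 concedes a survival bias that would understate the effect of the disease, and calls it inherent to following a cohort.

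**The concern.** Taken as written, the sentence makes dropout the end of observation for all outcomes alike. For the Barthel scale and the other questionnaires this is hard to avoid, since somebody has to see the participant. For death it is not, because vital status can be known without a visit.

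At age 75 or over, leaving a study is plausibly linked to functional or cognitive decline, which also predicts death. Kaplan-Meier, log-rank and Cox in their standard form assume that people censored at a given time have the same future risk as those who stay. If dropouts are worse off, absolute 18-month mortality is understated. If infection also makes dropout more frequent, more of the exposed group's later deaths and losses of function go unseen, and the comparison moves towards no difference.

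This cannot be left to the analysis plan, because a model cannot recover death dates that were never collected.

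**Working it through.** **1. The plan's own figure.** Section 2.2.3.2 gives a probability of 47% of staying below a 5-point change in the unexposed. I read the decrease of 10% as percentage points, giving 37% in the exposed, and the test as two-sided at 0.05.
- Hazard ratio (HR) = ln(0.37)/ln(0.47) = 1.317.
- Events (Schoenfeld, one third exposed) = (1.960 + 0.842)² / [(1/3)(2/3)(ln 1.317)²] = 467.
- Mean event probability = (2 × 0.53 + 0.63)/3 = 0.563, so N = 467/0.563 = 829.
- With 20% dropout: 829/0.80 = 1,037, against 1,035 stated.

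The figure is reproduced, though not uniquely: a two-proportion formula gives 861 × 1.2 = 1,034. By either route, the 20% only adds people to replace lost information.

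**2. How many people the rule touches.** 0.20 × 1,035 = 207 (138 unexposed, 69 exposed) if the allowance is used in full and equally. At the plan's own risks of functional change, 0.53 × 138 + 0.63 × 69 = 73.1 + 43.5, or about 117 of them, would have a change by 18 months, some of it after leaving.

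**3. Worst-case bounds for function.** Suppose 20% of each group is unobserved and the observed have risks of 53% and 63%.
- Unexposed: 0.8 × 0.53 = 42.4%, up to 42.4 + 20 = 62.4%.
- Exposed: 0.8 × 0.63 = 50.4%, up to 70.4%.
- Difference: from 50.4 − 62.4 = −12 points to 70.4 − 42.4 = +28 points.

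These are logical limits, not expectations.

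**4. Illustration with assumed rates.** Let p be a group's true 18-month risk, d its dropout proportion, and R the ratio of dropouts' risk to completers' risk. Completers' risk = p/(1 − d + dR). The values of R, the split of dropout and the mortality risks (10% unexposed, 13% exposed) are assumptions. Each split averages 20% at 2:1, for example (2 × 17.5 + 25)/3 = 20.

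| Dropout unexposed / exposed | R | Function: difference in points (HR); true 10.0 (1.32) | Mortality: difference in points; true 3.0 | Mortality risk ratio; true 1.30 |
|---|---|---|---|---|
| any of the three | 1.0 | 10.0 (1.32) | 3.0 | 1.30 |
| 20% / 20% | 1.5 | 9.1 (1.29) | 2.7 | 1.30 |
| 17.5% / 25% | 1.5 | 7.3 (1.23) | 2.4 | 1.26 |
| 15% / 30% | 1.5 | 5.5 (1.17) | 2.0 | 1.22 |
| 20% / 20% | 2.0 | 8.3 (1.28) | 2.5 | 1.30 |
| 17.5% / 25% | 2.0 | 5.3 (1.17) | 1.9 | 1.22 |
| 15% / 30% | 2.0 | 2.4 (1.07) | 1.3 | 1.15 |

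Example: 0.53/(1 − 0.175 + 0.175 × 1.5) = 0.53/1.0875 = 0.487, and 0.63/1.125 = 0.560, a difference of 7.3 points.

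**5. Deaths not seen.** The share of deaths among dropouts is dR/(1 − d + dR). At d = 0.20 it is 0.30/1.10 = 27% for R = 1.5, 0.40/1.20 = 33% for R = 2 and 0.60/1.40 = 43% for R = 3. Absolute mortality is understated by less: by 1 − 1/1.10 = 9% for R = 1.5 and 1 − 1/1.20 = 17% for R = 2.

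Steps 4 and 5 compare completers with everyone enrolled. In the planned analysis dropouts also contribute time up to censoring, and that estimator was not evaluated. The figures show direction and rough scale only.

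**The case against.** The strongest reply is that following each person to 18 months or dropout is how any cohort analysed by Kaplan-Meier and Cox is described, and that a journal article is a condensed document. The definition of dropout and the source of death dates may stand in the full protocol or in the data management plan that section 2.3 mentions. This stands in part: it cannot be said that later deaths will be lost. But the article does more than stay silent. It fixes when observation ends, with no exception for death.

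The other mitigations fall short. Assigned nurses may hold dropout below 20%, and may well hear of later deaths, but the text does not tell them to record these. The limitation in section 3.1 has the same direction, yet it is presented as inherent and given no remedy. Loss of deaths after dropout can be avoided.

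Three stronger readings are tempting and are not supported:
- A reader might infer that visits take place solely at the consultation or home, so that someone entering a nursing home is censored at that point. The text contains no such restriction. Home may cover the place where the person then lives, and non-institutionalisation is an entry condition only.
- A reader might conclude that the results are biased. Bias needs dropout related to outcome; with R = 1 there is none. With equal dropout in the two groups and the same R, the mortality risk ratio is unchanged.
- A reader might construct a case in which a true mortality risk ratio of 1.06 to 1.11 is seen as 1.00, by setting retained mortality at 12% in both groups and dropout at 25% against 17.5%. The 1.00 is then put in by assumption, because the whole effect has been placed among dropouts.

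Scale also matters. In the mortality illustration the loss is 0.3 to 1.7 points, while the standard error of the difference with 690 and 345 people is √(0.10 × 0.90/690 + 0.13 × 0.87/345) = 2.1 points.

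**Conclusion.** The point holds in conditional form. The stated rule ends follow-up at dropout for every outcome, including death; no later ascertainment of vital status is named; and up to 207 of 1,035 older people are expected to drop out. If dropout is related to decline, censoring is informative: 18-month mortality may be underestimated, and the exposed-unexposed comparison may be attenuated, mainly if dropout differs between the groups.

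The article gives no rates from which to fix the size. Under the assumed R of 1.5 to 2, the planned 10-point difference in function falls to between 9.1 and 2.4 points, and an assumed 3-point mortality difference to between 2.7 and 1.3. The low ends need both R = 2 and twice as much dropout among the exposed. The sample size is not in question.

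**What to change.** Separate two events in section 2.2.3.5: the end of study visits and the end of follow-up. Then:
- Unless the participant withdraws consent to use of the record, take vital status and date of death from the primary care record up to 18 months for every enrolled participant. Also take any Barthel score and any date of institutionalisation already recorded there.
- Analyse mortality on all enrolled participants to 18 months.
- Define dropout, and state that a move to a residence does not by itself end follow-up.

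The assigned nurse should make this look-up directly at month 18. The population-based extraction may not serve: its variable list (section 2.2.2.3) does not name mortality, and it runs to 2023 (section 2.2.2.4), whereas anyone enrolled after June 2022 reaches month 18 after December 2023.

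The cost is a few extra REDCap fields and a sentence in the protocol and the consent form. The number of participants does not change. The change largely closes the gap for mortality. For function it helps only where a Barthel score happens to be on record, so informative dropout remains a limitation to report there.

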##### 2.2.3.6 Analysis

Population characteristics will be described with their relevant 95% CI. The baseline characteristics will be compared between both groups upon enrolment. Kaplan-Meier survival curves will be generated for the main variables, which will be compared using the log-rank test. Cox models will be generated to study the impact of infection on the outcome variables at 6, 12, and 18 months and to adjust for sociodemographic and clinical characteristics of interest.

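### In the 18-month cohort, survival methods are the only group comparison named for five repeated scores seen at three follow-up visits; a longitudinal model would use the collected data better

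*Protocol article*

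**What the plan says.** The variables section (2.2.3.4) lists six outcomes: "The outcome variables will be mortality, functionality (Barthel scale), quality of life (EuroQol-5D), mental health (Hamilton depression rating scale"), followed by the Mini-Mental State Examination and the Frailty index. Mortality is the only one that is an event by nature; the other five are scores.

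The data collection section (2.2.3.5) fixes when they are seen: "Variables will be collected at four time points, namely at the baseline and at 6, 12, and 18 months". Follow-up "will comprise a period of 18 months for each participant or until their dropout"; death is not mentioned there.

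Beyond description and a comparison of baseline characteristics, the analysis section (2.2.3.6) names two methods. One is "Kaplan-Meier survival curves will be generated for the main variables, which will be compared using the log-rank test", where the main variables are not identified. The other is "Cox models will be generated to study the impact of infection on the outcome variables at 6, 12, and 18 months", with adjustment for covariates and no restriction to mortality.

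The sample size section (2.2.3.2) shows that a score is meant to be handled as a survival time: "Based on the assumption of a proportional hazards model for survival times, the sample size was estimated to allow the comparison of two curves". Its event-free state is a small functional change: "The probability of a change in functionality of < 5 points at 18 months was previously estimated to be 47% in the unexposed group", and "this figure was considered to decrease by at least 10% in exposed patients".

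**The concern.** A score measured at four visits can fall, recover and fall again. To enter a Kaplan-Meier or Cox analysis it must be replaced by the first visit at which it has crossed a cut-off. Three things follow.

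- **Information.** A small loss just past the cut-off counts the same as a large one, and later recovery is ignored. The second aim of the study concerns frailty, functional and cognitive capacity and quality of life, so five of the six outcomes are affected.
- **Timing.** A crossing is known only to lie between two visits six months apart. All crossings therefore share three event times, whereas the named methods are built for continuous time.
- **Death.** Participants are 75 or older, and mortality is itself an outcome. Unless something else is specified, these methods censor a participant who dies before a decline is seen. If infection raises mortality and the frailest are both likelier to decline and likelier to die, the functional comparison is pulled towards no effect.

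**Working it through.** **1. The planned number reproduces.** Inputs from section 2.2.3.2: 47% event-free in the unexposed, a decrease of 10 percentage points (the reading that reproduces the total), 2:1 ratio, two-sided 5%, 80% power, 20% dropout.

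- HR = ln(0.37)/ln(0.47) = 1.317; ln HR = 0.2752.
- Events = (1.960 + 0.842)² / [(2/3)(1/3)(0.2752)²] = 466.2.
- Mean event probability = (2/3)(0.53) + (1/3)(0.63) = 0.563.
- 466.2/0.563 = 827.6 evaluable; divided by 0.8 = 1,034.5, rounded up to 1,035, the article's figure.

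So the design does rest on a dichotomised functional change treated as a survival time.

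**2. Where the events fall.** With 828 evaluable (552 unexposed, 276 exposed) and a constant hazard (assumption), the risk per visit interval is 1 − 0.47^(1/3) = 0.2225 and 1 − 0.37^(1/3) = 0.2821.

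| Visit | Unexposed | Exposed | Tied events |
|---|---|---|---|
| 6 months | 122.8 | 77.9 | about 201 |
| 12 months | 95.5 | 55.9 | about 151 |
| 18 months | 74.2 | 40.1 | about 114 |

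Maximising the Cox partial likelihood on these counts:

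- Breslow ties: log-HR 0.2373, HR 1.268. The log-HR is 1 − 0.2373/0.2752 = 14% too small.
- Efron ties: HR 1.314.
- Grouped-time complementary log-log model: HR 1.317, the true value.

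**3. Information kept.** Dichotomising one normal score at the 47% point keeps φ(z)²/[p(1 − p)] = 0.635, a loss of about 36%. For the actual visit pattern, simulation assumed normal scores, a linear decline with varying slopes, and a cut-off set so that 53% and 63% cross by 18 months (552 and 276 participants). The log-rank test on first crossing was compared with a baseline-adjusted analysis of the 18-month score. Information kept is the squared ratio of the mean test statistics.

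| Measurement-error SD (baseline SDs) | Mean z, log-rank | Mean z, score | Information kept | Power, log-rank / score |
|---|---|---|---|---|
| 0.3 | 2.90 | 3.68 | 62% | 0.81 / 0.96 |
| 0.6 | 2.77 | 4.05 | 47% | 0.78 / 0.99 |
| 1.0 | 2.69 | 4.46 | 36% | 0.78 / above 0.99 |

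The loss is thus roughly 36–64%. The article gives no measurement error, and ceiling effects on Barthel could move the figure either way.

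**4. Death, if censored by default.** Assumptions: 10% mortality at 18 months in the unexposed, decline seen only at visits, and a gamma frailty shared by decline and death. The true gap in functional decline is 10.0 points. Apparent gaps are below; repeat runs differ by up to about 0.2 points.

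| Frailty variance | Mortality HR 1.5 | HR 2 | HR 3 |
|---|---|---|---|
| 0 | about 10 | about 10 | about 10 |
| 0.25 | 9.7 | 9.4 | 9.0 |
| 1 | 9.5 | 8.9 | 7.6 |

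At mortality HR 1 there is no attenuation at any of these variances.

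Absolute risks also shift. With independent hazards a (decline) and b (death) over 18 months, cumulative incidence is [a/(a + b)](1 − e^−(a+b)). For 15% mortality in both groups, the Kaplan-Meier risks of 0.53 and 0.63 correspond to cumulative incidences of 0.49 and 0.59. If mortality in the exposed has HR 2, their 0.63 becomes 0.55.

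**5. Decline-or-death is not a neutral substitute.** Without frailty and with equal 10% mortality, the gap becomes (0.47 − 0.37) × 0.9 = 9.0 points. At mortality HR 3 it is 0.47 × 0.9 − 0.37 × 0.9³ = 0.423 − 0.270 = 15.3 points.

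**The case against.** - **Most of the information is lost.** A reader might infer this, but it is not established. A single split keeps about 64%, and in the simulation the loss passes half only with noisier measurement. For the sized endpoint, 80% power already allows for the dichotomy, so a score analysis adds power beyond the plan; nothing planned is lost. This stands.
- **The hazard ratio will be attenuated.** A reader might infer this from the ties. The article names no tie method, and with Efron the bias is negligible. The choice may sit in an analysis plan. This stands.
- **The plan treats death as non-informative censoring.** A reader might infer this from the named methods. Nowhere does the article say that deaths are censored. Its limitations section (3.1) recognises a survival bias that would understate the effect of the disease. Only the default behaviour of the methods can be discussed, and the resulting bias needs both shared frailty and excess mortality in the exposed. This stands.
- **Details may be elsewhere.** Cut-offs for the four scores other than Barthel, and the meaning of the main variables, may be in a fuller document. Their absence is not the point here, and the Kaplan-Meier sentence cannot be assumed to cover every score. The Cox sentence, however, does reach the outcome variables without restriction. The choice of method is therefore stated in the article.
- **Time to a 5-point Barthel loss matches the sample size.** True, and a reason to keep that endpoint. It does not justify survival analysis as the only comparison for the other four scores.

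**Conclusion.** The point holds as a worthwhile and inexpensive improvement, in limited form. The stated methods are right for mortality and ill-suited as the only group comparison for five repeated scores. The information given up is substantial, roughly 36–64% under normal scores and linear decline. The grouping of about 466 functional events on three visits is certain in kind; the counts per visit assume a constant hazard. Its harm is modest: HR 1.27 against 1.32 with Breslow, and almost none with Efron or a grouped-time model. The handling of death is unstated. Default censoring could understate functional harm by about 0.5 to 2.4 points of a 10-point gap at frailty variance 1 and mortality HR 1.5 to 3, and by nothing at zero frailty or equal mortality. The mortality and frailty values are assumptions, not figures from the article.

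**What to change.** Revise section 2.2.3.6 as follows.

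1. Mortality: keep Kaplan-Meier, log-rank and Cox.
2. Barthel, EuroQol-5D, Hamilton, Mini-Mental and Frailty index: a mixed model for repeated measures with exposure, visit and their interaction, adjusted for the baseline score and the planned covariates. Report the exposure contrast at 6, 12 and 18 months from one model per score.
3. Sized endpoint (Barthel change of at least 5 points): keep it, fitted with a grouped-time complementary log-log model on the three visits, or Cox with Efron or exact ties.
4. Death: state how it enters the functional analyses. Add cumulative incidence with death as a competing event, and decline-or-death, as supporting analyses. The composite should not lead, because it changes the quantity on which the study was sized. The mixed model alone does not resolve truncation by death, since it treats scores after death as missing data.
5. State which Barthel analysis leads.

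Cost: analysis wording and modest extra work in standard software, with no new visits or participants. The fit of a linear model must be checked for scores with ceiling effects.

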#### 2.2.4 Qualitative study with a critical social approach

##### 2.2.4.1 Participants

Clinical nurses will invite to participate subjects ≥75 years of age with a specific profile, who are already part of the cohort study, together with their family caregivers. Caregivers with < 6 months as such at the beginning of the pandemic will be excluded, as well as those with sensory or cognitive deficits. Sample selection will be intentional (based on the study aim) although, depending on the emerging development of the study, it will develop toward a theoretical sampling approach.

The sample size for each of the participating regions has been estimated to be about 40 interviews of individuals ≥75 years of age and the focus groups will include 6–10 family caregivers.

##### 2.2.4.2 Data collection

Data will be obtained from semi-structured interviews of healthcare users ≥75 years old and focus groups of caregivers. In the interviews, there will be the same proportion of men and women, and two age groups, from 75 to 84 years and over 85. In the case of groups, the criterion for homogeneity will consist of being a live-in caregiver or not and the criteria for heterogeneity will be age, gender, and years as a caregiver. The interviews and focus groups will follow a predefined script, which will be revised as the analysis process progresses. The duration of interviews is estimated to be 1 h, and the focus groups will last 2 h. Both will be conducted in an accessible place and will be audio-recorded and transcribed.

In order to compare the results between the different regions, the interview guide and the dimensions to be studied were agreed upon by the coordinating team, experts in qualitative methodology. Both, the interviews and the analysis, will be carried out by this same team, which will act in a coordinated manner and share all the information throughout the process, thus ensuring methodological homogeneity in all areas.

##### 2.2.4.3 Analysis

The analysis will be thematic, complemented by a semiotic analysis, with inductive and deductive elements, identifying units of meaning and assigning codes that will be grouped into categories. An analysis of discursive positions will be carried out, considering the roles that condition the topic. Finally, the discourse will be analyzed as a reflection of ideological positions (inequality and domination). The results will be presented as the participants' verbatims together with the interpretation by the researchers. A reflective diary will be kept for which triangulation of techniques and researchers have been contemplated. Transferability will be ensured by the exhaustive and accurate description of the context, the participants, and their perspectives.

